### 2.10. Sample Size Calculation

The primary endpoint is the within-participant difference in specificity for detecting clinically significant prostate cancer (csPCa; ISUP ≥ 2) within the PI-RADS 3–4 decision zone, comparing standard PI-RADS v2.1 assessment (test-positive defined as PI-RADS 4; test-negative as PI-RADS 3) versus the PROS-TD-AI-assisted recommendation (positive = “recommend 4”; negative = “recommend 3”). All eligible PI-RADS 3–4 examinations will undergo MRI-targeted biopsy (±systematic biopsy per local protocol) within a prespecified time window, providing complete histopathological verification for the primary analysis. We powered this study to detect an absolute specificity improvement of 0.10 (two-sided alpha = 0.01; 80% power) using a paired-proportions (McNemar) approach applied to the non-csPCa subgroup. Let p10 denote the proportion of non-csPCa participants classified as positive by PI-RADS (4) but negative by PROS-TD-AI (3) (false-positive→true-negative), and p01 denote the reverse discordance. Under conservative, prespecified discordant-pair assumptions (p10 = 0.15; p01 = 0.05; net delta = p10 − p01 = 0.10; total discordance = p10 + p01 = 0.20), the required number of non-csPCa participants is computed as follows: n_non-csPCa = ((z_(1−alpha/2) + z_(1−beta))^2^ × (p01 + p10))/(p10 − p01)^2^. Using z_(1−alpha/2) = 2.576 and z_(1−beta) = 0.842 gives n_non-csPCa ≈ ((2.576 + 0.842)^2^ × 0.20)/0.10^2^ ≈ 234 [49]. To convert this to the total sample size, we used the PROMIS trial as an external prevalence benchmark; PROMIS reported 220/576 = 38% (95% CI 34–42) clinically significant cancer on template mapping biopsy [6]. For conservative planning, we assumed 38% (the proportion of ISUP csPCa, thus 62% non-csPCa), yielding N_total = 234/0.62 ≈ 378 PI-RADS 3–4 participants. We will inflate this by 10–15% for exclusions and non-evaluable examinations, resulting in a planned enrollment of approximately 420–445 participants (target ~450). This target also satisfies empiric minimum sample sizes proposed for objective testing of AI binary classification performance metrics (including ROC AUC), where an empirical minimum sufficient test sample size of approximately 400 studies has been reported [50].

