### 2.2. Study Population

Consecutive patients with clinical suspicion of PCa—defined as an elevated prostate-specific antigen (PSA) level > 4 ng/mL, an abnormal digital rectal examination, or both, without prior prostate biopsy—will be recruited from outpatient clinics. Eligibility criteria, key contraindications, and the imaging workflow, including acquisition of the TDD sequence, are summarized in Figure 1. All participants will provide written informed consent prior to enrollment.

According to the local standard-of-care diagnostic pathway, men with clinical suspicion of PCa undergo mpMRI (including T2-weighted (T2W), diffusion-weighted (DWI), and dynamic contrast-enhanced (DCE) sequences). The dominant and any additional PI-RADS ≥ 3 lesions are scored by a senior radiologist with at least 10 years of experience using the PI-RADS v2.1 system:PI-RADS 1: Very low (clinically significant cancer highly unlikely).PI-RADS 2: Low (clinically significant cancer unlikely).PI-RADS 3: Intermediate (equivocal).PI-RADS 4: High (clinically significant cancer likely).PI-RADS 5: Very high (clinically significant cancer highly likely).

Patients with PI-RADS 1–2 findings are not offered biopsy, while those with PI-RADS 3–5 lesions undergo prostate biopsy as per standard of care, following the Ginsburg protocol [36]. Biopsy results are interpreted according to the EAU–EANM–ESTRO–ESUR–ISUP–SIOG guidelines [2] and serve as the diagnostic reference standard for this study.

For the purpose of this study, all enrolled patients will undergo an additional 4.5-minute TDD sequence during the same visit as the standard mpMRI. All image data will be exported to a dedicated database. Only standard-of-care mpMRI sequences will be stored in the institutional Picture Archiving and Communication Systems (PACS) for clinical use. We will report baseline clinical and imaging characteristics (e.g., age, PSA, PSA density, prostate volume, prior MRI findings, and scanner/protocol variables) for the full cohort and, where applicable, by analysis split (training/validation/test) and by PI-RADS category.

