The primary endpoint is the paired improvement in specificity (non-csPCa correctly recommended as “3”) of PROS-TD-AI-assisted recommendations versus standard PI-RADS (4 vs. 3), tested using McNemar’s test [49], in the non-csPCa subgroup (two-sided alpha = 0.01). The secondary endpoints include paired sensitivity in csPCa (McNemar), upgrade/downgrade reclassification rates stratified by pathology, and continuous-score discrimination (ROC AUC) and calibration (*p* < 0.05 for secondary analyses). We will present 2 × 2 cross-tabulations (index test vs. reference standard) for PI-RADS and PROS-TD-AI recommendations in the biopsy-verified PI-RADS 3–4 cohort, including counts of TP, FP, TN, and FN. Baseline demographic, clinical, and technical characteristics will be summarized for each analysis split (training/validation/test and the prospective evaluation cohort) to assess representativeness and potential distribution shift, including age, PSA/PSA density, prostate volume, PI-RADS category, and key acquisition variables (scanner/vendor and sequence quality markers). Because participants are consecutively enrolled within the routine intended-use pathway (biopsy-verified PI-RADS 3–4), we expect the csPCa prevalence to reflect this clinical setting. We will report the observed csPCa prevalence and discuss any material deviation as potential spectrum effects affecting generalizability.

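### The ~450 target is derived in PI-RADS 3–4 men, but section 2.2 enrols men before the MRI is read; sections 2.2, 2.9 and 2.10 use different denominators

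*Protocol article*

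**What the plan says.** Section 2.10 sets the design target: "We powered this study to detect an absolute specificity improvement of 0.10 (two-sided alpha = 0.01; 80% power"). It takes discordance rates of "p10 = 0.15; p01 = 0.05" among men without csPCa, which gives 234 such men. It then converts to all PI-RADS 3–4 men: "we assumed 38% (the proportion of ISUP csPCa, thus 62% non-csPCa"), "yielding N_total = 234/0.62 ≈ 378 PI-RADS 3–4 participants". The only further step is a 10–15% allowance for exclusions and non-evaluable examinations, "resulting in a planned enrollment of approximately 420–445 participants (target ~450").

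Section 2.2 describes who is enrolled. Consecutive men come from outpatient clinics because of a raised PSA, an abnormal DRE or both, and consent before enrolment. Then "all enrolled patients will undergo an additional 4.5-minute TDD sequence during the same visit as the standard mpMRI". After the read, "Patients with PI-RADS 1–2 findings are not offered biopsy", while men scored 3–5 are biopsied.

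Section 2.9 confines diagnostic performance to the biopsy-verified PI-RADS 3–4 cohort. It describes enrolment differently from 2.2: "Because participants are consecutively enrolled within the routine intended-use pathway (biopsy-verified PI-RADS 3–4").

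**The concern.** In section 2.2 a man is enrolled before his MRI is scored. Some enrolled men will be read as PI-RADS 1–2 and have no biopsy. Others will be read as PI-RADS 5 and fall outside the 3-versus-4 comparison. Neither group can contribute to the primary McNemar test.

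The conversion in 2.10 has no step for them. The five non-evaluability conditions in section 2.3 are incomplete MRI, failed TDD acquisition, artefact, failed segmentation, and missing biopsy within the PI-RADS 3–4 cohort. A score of 1–2 or 5 is not among them.

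The target governs when recruitment stops. If the study team counts every enrolled man towards ~450, the subgroup for the primary test will be smaller than the 234 the plan requires. A shortfall found after recruitment has closed is hard to repair. If the team counts only PI-RADS 3–4 men, the test keeps its power, but the enrolment and scanning load is larger than the figure called planned enrolment.

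**Working it through.** **Inputs from section 2.10:** two-sided alpha 0.01 (z = 2.576), power 80% (z = 0.842), p10 = 0.15, p01 = 0.05, non-csPCa share 0.62, allowance 10–15%, target ~450.

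**Input not in the document:** f, the share of men enrolled under 2.2 who score PI-RADS 3–4. It is assumed here, over the range 0.4 to 0.9.

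**1. Reproducing the plan's figures.**
- n = (2.576 + 0.842)² × 0.20 / 0.10² = 233.7, so 234.
- 234 / 0.62 = 377.4, so 378.
- 378 / 0.90 = 420 and 378 / 0.85 = 444.7, so 445.

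Every stated number is confirmed.

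**2. If ~450 counts only PI-RADS 3–4 men.** With 15% non-evaluable, 450 × 0.85 × 0.62 = 237 men without csPCa. Power = Φ(0.10 × √237 / √0.20 − 2.576) ≈ 81%. With 10% non-evaluable there are 251 men and power is about 83%.

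**3. If ~450 counts all men enrolled under 2.2.** The share f needed to leave 378 evaluable PI-RADS 3–4 men is 378 / (450 × e), where e is the evaluable share:
- no losses: 378 / 450 = 84%
- 10% non-evaluable: 378 / 405 = 93%
- 15% non-evaluable: 378 / 382.5 = 99%

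The whole margin is 450 − 378 = 72 men. It would have to cover every PI-RADS 1–2 and 5 man as well as all technical failures and missing biopsies.

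**4. Power under assumed shares.** Non-csPCa n = 450 × f × e × 0.62, and power = Φ(0.10 × √n / √0.20 − 2.576). Worked case, f = 0.6 and e = 0.90: n = 150.7; Φ(2.745 − 2.576) = Φ(0.169) = 56.7%. In each cell the first figure is for 10% non-evaluable and the second for 15%.

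| Assumed f | Non-csPCa n from 450 enrolled | Power | Men to enrol for 378 evaluable, 378/(f × e) |
|---|---|---|---|
| 0.9 | 226 / 213 | 78.4% / 75.5% | 467 / 495 |
| 0.8 | 201 / 190 | 72.4% / 69.3% | 525 / 556 |
| 0.7 | 176 / 166 | 65.1% / 62.0% | 600 / 636 |
| 0.6 | 151 / 142 | 56.7% / 53.6% | 700 / 742 |
| 0.5 | 126 / 119 | 47.2% / 44.4% | 840 / 890 |
| 0.4 | 100 / 95 | 36.9% / 34.5% | 1,050 / 1,112 |

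**5. Sensitivity to the power formula.** The table uses the plan's own normal approximation. Summing binomial probabilities for the asymptotic McNemar test gives 82.8% rather than 80.1% at n = 234, and 81.1% rather than 78.4% at n = 226. The top row is therefore borderline. At f = 0.8 that method gives 75.1% / 71.9%, and at f = 0.4 it gives 35.4% / 33.0%, so the pattern does not change.

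**The case against.** The strongest reply is that 2.10 keeps one unit throughout. The 10–15% is applied to a count of PI-RADS 3–4 men, so the natural product is also a count of PI-RADS 3–4 men. The parenthesis in 2.9 supports this. On that reading nothing is lost: about 237 men without csPCa and about 81% power. This stands as a legitimate reading of 2.9 and 2.10. It does not fit 2.2, where a man is enrolled before he can be scored, let alone biopsied.

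A reader might go further and infer that the study is underpowered, or that the sample-size arithmetic is wrong. The documents support neither. The arithmetic reproduces exactly. No section says that recruitment stops at 450 men scanned. The PI-RADS 3–4 share is not stated, so every power figure below 80% depends on one reading and an assumed share.

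Two other points carry some weight. Figure 1 holds the study flow and was not available for this check; it may show where PI-RADS 1–2 and 5 men leave the counted cohort. A condensed article may also leave the number to be scanned to the full protocol, so its absence alone is no fault. Neither point removes the conflict between what 2.2 and 2.9 say enrolment is, or tells the reader which meaning 2.10 uses.

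The word exclusions in the 10–15% could be stretched to cover PI-RADS 1–2 and 5 men. With 72 men in the whole margin, that would require almost every enrolled man to score 3 or 4.

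**Conclusion.** The point holds as an inconsistency in the enrolment unit, not as an arithmetic error. Sections 2.2, 2.9 and 2.10 do not use the same denominator, and the meaning of ~450 decides whether the stated power applies.

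If ~450 counts all men enrolled as 2.2 describes, 80% power needs about 93–99% of them to score PI-RADS 3–4 with 10–15% non-evaluable. At assumed shares of 40–90%, power lies between 34.5% and 78.4%. If ~450 counts only PI-RADS 3–4 men, power is about 81%, and the number to enrol and scan exceeds 450.

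These figures take as given the plan's discordance rates, its 62% non-csPCa share, its 10–15% allowance and its power formula. That the sections conflict is certain; a loss of power is conditional.

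**What to change.** In 2.10, state that ~450 is the number of PI-RADS 3–4 participants counted after the MRI read, intended to leave 378 evaluable and biopsy-verified men, of whom 234 are without csPCa. The 450 already contains the non-evaluable allowance, so it should not be labelled the evaluable number. Add the expected number to be enrolled and scanned as 450 divided by the site's PI-RADS 3–4 share. For assumed shares of 90% down to 40% that is 450 / 0.9 = 500 up to 450 / 0.4 = 1,125.

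If ~450 is instead the ceiling for all enrolled men, restate the power for the expected number without csPCa, using the site's share.

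In either case, make 2.2, 2.9 and 2.10 use one denominator, with separate terms for men enrolled before MRI and men counted in the PI-RADS 3–4 cohort.

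The cost is a few sentences and one local estimate, the share of men scanned for suspicion who score PI-RADS 3–4. More scans are needed only if ~450 was meant as the total enrolled and the sponsor wants to keep 80% power.

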### 2.11. Cross Validation

All model development will use patient-level, stratified, grouped cross-validation to prevent data leakage: all images, sequences, lesions, and derived patches from a given patient will be assigned to a single fold only (no lesion/slice-level splitting). Folds will be stratified by csPCa status (ISUP ≥ 2) (and, where feasible, by PI-RADS category) to preserve class balance. Any data-dependent pre-processing and model selection steps (e.g., normalization/scaling, imputation, feature selection, threshold tuning, and calibration) will be performed exclusively within the training folds and then applied unchanged to the corresponding validation folds. The prospective cohort will be reserved for final evaluation only and will not be used for training, hyperparameter tuning, or threshold selection. The final model will be locked prior to prospective enrollment.

## 3. Expected Results

### 3.1. Deep Learning Models

We anticipate the development of two complementary deep learning models for automated prostate analysis:Prostate Segmentation Model: Based on U-Net or ProGNet architectures, initially trained on the PI-CAI dataset [39] and subsequently fine-tuned using multiparametric MRI (mpMRI) data from the Clinical Hospital of the University of Chile (HCUCH). This model is expected to accurately delineate the prostate gland and serve as a pre-processing step for downstream microstructural analysis. For the segmentation task, a Dice similarity coefficient of ~0.92 is an a priori target informed by the prior literature; observed segmentation performance will be reported accordingly.Tissue Microstructure Estimation Model: Employing a transformer-based architecture inspired by sparse representation techniques; METSC [47], this model will estimate voxel-wise tissue microstructural parameters—including intracellular and extracellular volume fractions and diffusivities—from multi-shell diffusion MRI (dMRI) data. These microstructural parameters will then be used for tissue classification. For microstructure estimation and lesion classification, we hypothesize clinically meaningful discrimination and will report AUC, accuracy, sensitivity, specificity, and 95% confidence intervals in the final study report. Any numerical performance figures stated here are a priori targets informed by the prior literature rather than observed outcomes.

Together, these models will form a fully automated pipeline integrating anatomical and microstructural information to support clinical decision-making in PCa diagnostics.

### 3.2. Pipeline Integration

We propose an end-to-end deep learning pipeline that combines anatomical segmentation with microstructure-based tissue classification. The pipeline will be trained end-to-end using a deep neural network that combines imaging data with clinical features, thereby simultaneously optimizing segmentation and classification objectives. This joint learning approach enables shared feature representation, enhancing both anatomical delineation and microstructural characterization. By integrating diffusion-informed biomarkers with anatomical information, this framework is expected to improve diagnostic accuracy and provide clinically meaningful predictions.

## 4. Discussion

This protocol is designed to prospectively develop and evaluate novel imaging techniques and analytic approaches aimed at improving non-invasive detection of csPCa. By integrating time-dependent diffusion MRI (TDD-MRI) with AI-based quantitative analysis, this study seeks to enhance diagnostic specificity, reduce the reliance on invasive biopsy procedures, and provide accurate, low-risk, and more accessible risk stratification for men at intermediate clinical risk.

Demonstrating higher specificity and reliable performance of these novel imaging methods could have a significant impact on both research and clinical practice. Positive findings would provide a foundation for future randomized controlled trials and support evidence-based updates to current standard-of-care diagnostic workflows, potentially leading to more personalized and efficient patient management.

PROS-TD-AI may offer its greater incremental clinical value in diagnostic scenarios where mpMRI interpretation is most equivocal and PI-RADS exhibits lower specificity, particularly for PI-RADS 3–4 [51] lesions and transition-zone/central gland abnormalities, in which benign prostatic hyperplasia and stromal changes can closely mimic clinically significant disease [9]. In these settings, the addition of TDD-derived microstructural biomarkers and quantitative AI-based analysis may improve discrimination and reduce inter-reader variability, thereby refining risk stratification around biopsy decision thresholds and potentially decreasing unnecessary biopsies without compromising sensitivity for csPCa diagnosis.

In addition to advances in non-invasive cancer detection techniques, there is a growing trend toward biparametric MRI (bpMRI) over mpMRI to reduce scan duration, lower costs, and avoid gadolinium without losing accuracy. The multicenter PRIME trial showed non-inferiority of bpMRI for detecting csPCa compared to mpMRI (29.2% vs. 29.6%, respectively), with 99% adequate quality scans, aligning with wider evidence that contrast-free protocols can maintain accuracy while improving efficiency [52,53,54]. Nevertheless, this study retains mpMRI (including DCE) as the guideline-concordant reference for model development and evaluation. Given that TDD-MRI does not require contrast, it could strengthen future bpMRI protocols by adding microstructural information; training AI on bpMRI + advanced diffusion is a promising future direction. Prospective head-to-head studies and external validation are still needed to confirm whether contrast-free pipelines can match or surpass mpMRI in routine clinical practice.

From an implementation standpoint, several barriers may influence the clinical adoption of this approach. The TDD sequence was developed and optimized on a specific 3.0 T scanner platform (Skyra, Siemens Healthcare), and its portability to other scanners, vendors, field strengths, or acquisition environments may require sequence harmonization, rigorous quality control, and external validation. In addition, TDD-derived microstructural estimates can vary with scanner hardware and vendor-specific implementation details, gradient performance, and acquisition settings, as well as with signal quality and motion sensitivity; these factors may affect quantitative feature stability and limit transportability of models trained under a single configuration. To mitigate these risks, the protocol prespecifies acquisition standardization, systematic quality control procedures, and detailed reporting of scanner characteristics and acquisition parameters to support interpretability, replication, and future multi-site evaluation. In addition, successful deployment will depend on adequate computational resources and seamless integration into clinical workflows (e.g., PACS/viewer overlays and reporting), as well as training for radiologists and technologists to interpret risk scores and probability maps and to apply PROS-TD-AI recommendations appropriately. Other limitations include the single-center setting, potential spectrum effects inherent to a biopsy-verified PI-RADS 3–4 cohort, and the need for external multi-vendor validation before broad clinical adoption. As an observational study, PROS-TD-AI outputs will not modify management; therefore, downstream clinical impact will require future interventional evaluation.

This project emphasizes the translational value of basic and preclinical research into clinically actionable applications. By focusing on clinically meaningful endpoints, it bridges the gap between advanced imaging research and real-world patient care, supporting evidence-driven decision-making in prostate cancer management.

## Figures and Tables

**Figure 1 jimaging-12-00053-f001:**
[figure not shown]
Study flow and imaging protocols. Key exclusion criteria and contraindications are listed on the left. TDD-derived microstructural parameters will be extracted from all patients undergoing mpMRI. mpMRI, multiparametric MRI; TDD, time-dependent diffusion; PI-RADS, Prostate Imaging–Reporting and Data System; csPCa, clinically significant prostate cancer; non-csPCa, non-clinically significant prostate cancer.

## Data Availability

The original contributions presented in this study are included in the article and the Supplementary Materials. Further inquiries can be directed to the corresponding author.

## Abbreviations

The following abbreviations are used in this manuscript:

PCa	Prostate cancer
PSA	Prostate-specific antigen
DRE	Digital rectal exam
mpMRI	Multiparametric MRI
csPCa	Clinically significant prostate cancer
GS	Gleason score
ISUP	International Society of Urological Pathology
Non-csPCa	Clinical insignificant prostate cancer
TDD	Time-dependent diffusion
GG	Gleason grade
